#### Analysis set

2.8.2

The Full Analysis Set will be used for all primary analysis. Per Protocol Set analysis will be performed for evaluating the sensitivity of results.

#### Statistical analysis

2.8.3

Data management uses EXCEL software to build a database, double entry, check for outstanding values, and lock. Statistical analysis will be performed using SPSS 25.0 software for statistical analysis. The normality of the measurement data is tested. The data obeying the normal distribution is Student's t test, which is expressed by mean ± standard deviation. The data not obeying the normal distribution is rank sum test. And marginal homogeneity test; count data are expressed by rate and composition ratio, and comparison is performed by chi-square test; repeated measurement data are expressed by mean ± standard deviation, intra-group comparison is performed by analysis of variance of repeated measurement data, and inter-group comparison is by multivariate analysis of variance (MANOVA). *P* ≤ .05 indicates that the difference is statistically significant.

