### Secondary outcomes

2.7

The second outcome measure is based on TCM syndrome evaluation criteria.(1) Healing: The clinical symptoms and signs of TCM disappear or almost disappear, and the syndrome score is reduced by ≥90%; (2) Significant effect: The clinical symptoms and signs of TCM are obviously improved, and the syndrome score is reduced by ≥60%; (3) Effective: Chinese medicine Clinical symptoms and signs have improved, syndrome scores decreased by < 60%, but ≥30%; (4) Invalid: The clinical symptoms and signs of TCM were not improved, even worse, and the syndrome score was reduced by < 30%. Integral variation formula (Nimodipine method: [(pre-treatment score - post-treatment score) ÷ pre-treatment score] × 100%.

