#### Sample size

2.8.1

Based on the results of our previous study, the effective rate of CP/CPPS in the intervention group was P1 = 0.80. The PSD effective rate of the control group was P2 = 0.65 [(two-sided type I error rate of 0.05, α = 0.05); (one-sided type I error rate of 0.10, β = 0.10)]. Substituting f (α, β) into the formula is as follows: n1 = n2 = 10.5 × (0.8 × 0.2 + 0.65 × 0.35) ÷ 0.152 = 75. The lost follow-up rate of patients will be controlled at 10%, so an additional 8 cases are added to each group. n1 = n2 = 83, that is, 83 cases will be taken from each of the intervention group and the control group. According to Cohen, this effect size is considered “moderate”.

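### On its natural reading, section 2.8.3 compares the four ordered TCM response grades with a chi-square test that ignores their order; a rank-based comparison would suit the question better and costs one sentence

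*Protocol article*

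**What the plan says.** Protocol article, section 2.7: "The second outcome measure is based on TCM syndrome evaluation criteria". Four grades follow, each defined by the percentage fall in the syndrome score. The top grade is "1) Healing: The clinical symptoms and signs of TCM disappear or almost disappear, and the syndrome score is reduced by ≥90" per cent and the bottom grade is "4) Invalid: The clinical symptoms and signs of TCM were not improved, even worse, and the syndrome score was reduced by < 30" per cent. Between them lie a significant-effect grade (60% or more, below the top grade) and an effective grade (30% to under 60%). The order is built into the definition.

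Section 2.8.3 assigns tests by type of data, not by outcome:

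- Measurement data get a t test if normal; otherwise "The data not obeying the normal distribution is rank sum test".
- For categorical data, "count data are expressed by rate and composition ratio, and comparison is performed by chi-square test".
- Repeated measurements get analysis of variance within groups and MANOVA between groups.

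A marginal homogeneity test is also mentioned, in a fragment with no outcome attached. No trend test, ordinal model or rank test is assigned to graded responses.

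**The concern.** A four-grade response is normally tabulated as the percentage of each arm in each grade, that is, as a composition ratio. The only between-arm test the protocol gives for data shown that way is chi-square. On a table of two arms by four grades this is a Pearson test with 3 degrees of freedom, and it responds to any difference between the two distributions, including patterns that favour neither arm. The clinical question is narrower: do patients given acupuncture end up in better grades?

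At stake are the power of the only stated secondary efficacy outcome and whether its p-value answers that question. The type I error is not at stake, and neither is the primary outcome.

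**Working it through.** **1. Inputs.** From section 2.8.1: effective rates of 0.80 (intervention) and 0.65 (control), "two-sided type I error rate of 0.05, α = 0.05", 75 per arm before and 83 per arm after the allowance for loss to follow-up. The protocol gives no distribution over the four grades, so the control splits below are assumptions. Section 2.8.1 also does not tie its effective rate to the TCM grades; using it for the cut at 30% is a further assumption.

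**2. The plan's own figure.** Reading the printed divisor as 0.15 squared, the formula gives 10.5 × (0.16 + 0.2275) / 0.0225 = 180.8 per arm, not 75. That is a separate matter. Here 75 and 83 are used only as the numbers the trial would have.

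**3. What the test ignores.** Take an illustrative table, grades from best to worst: treated 20, 25, 20, 10; control 10, 20, 25, 20 (75 each). Expected counts are 15, 22.5, 22.5, 15 in each arm.

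- Chi-square = 2 × (25/15 + 6.25/22.5 + 6.25/22.5 + 25/15) = 7.78 on 3 df, p = 0.051.
- Rank sum: the mid-ranks are 15.5, 53, 98, 135.5. The treated rank sum is 310 + 1325 + 1960 + 1355 = 4950, against 75 × 151/2 = 5662.5 expected. The tie-corrected variance is (75 × 75/12) × (151 − 236100/22350) = 65,830, so z = −712.5/256.6 = −2.78, p = 0.005.

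Now reorder the same columns: treated 20, 20, 10, 25; control 25, 10, 20, 20. Chi-square is still 7.78, p = 0.051. The treated rank sum becomes 460 + 1210 + 905 + 3200 = 5775, so z = 112.5/256.6 = 0.44, p = 0.66. The chi-square p-value cannot tell a steady improvement from a pattern with almost no net shift.

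**4. Power under a shift across all grades.** The common odds ratio is (0.80/0.20) / (0.65/0.35) = 2.154, applied at every cut. Power was simulated at P ≤ 0.05 with an uncorrected 3-df chi-square and a tie-corrected rank sum test. Control splits are in per cent, best to worst.

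| Control split | n per arm | Chi-square, 3 df | Rank sum |
|---|---|---|---|
| 5/20/40/35 | 75 | 55% | 72% |
| 10/25/30/35 | 75 | 56% | 73% |
| 10/20/35/35 | 75 | 56% | 73% |
| 15/25/25/35 | 75 | 57% | 74% |
| same four splits | 83 | 60-62% | 76-78% |

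Simulation error moves these by a point or so. A more extreme split (2/13/50/35) gives 51% v 69% at 75 per arm. Under no difference both tests reject in about 5% of trials.

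**5. Power under other patterns** (75 per arm, control 10/25/30/35).

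- Partial shift, treated 15/28/37/20: chi-square 40%, rank sum 42%.
- Whole benefit between the two lowest grades, treated 10/25/45/20: chi-square 47%, rank sum 19%.

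**6. Two-level effective rate** (reduction of at least 30% v less). With 80% v 65%, the 2×2 chi-square has about 54% power at 75 per arm and 58-59% at 83, however the upper grades are split.

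**The case against.** Five arguments have weight.

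- **The test is inferred.** Section 2.8.3 names neither this outcome nor a test with 3 degrees of freedom. A reader might infer that the protocol prescribes one for the TCM grades; it does not say so. What stands is that chi-square is the only between-arm test offered for categorical data. That is a stated rule and not just detail left to an analysis plan.
- **The grades might be collapsed to an effective rate.** Section 2.8.3 mentions rates as well as composition ratios, and section 2.8.1 uses an effective rate. A 2×2 test on that rate has a direction and a readable difference. But neither section 2.7 nor 2.8.3 states the collapse, and under an even shift the 2×2 test has about 54% power against 72-74% for the rank sum test.
- **The rank sum clause might be meant to cover the grades.** Its wording is loose and the marginal homogeneity fragment follows it. But the clause continues the sentences on measurement data, and a marginal homogeneity test is for paired data and cannot compare two independent arms.
- **Direction is not lost.** A reader might infer that the analysis would leave the direction of effect unknown. It would not: composition ratios reported by arm would show it. What lacks direction is the test. A rank sum p-value gives no effect estimate either, which is why an odds ratio has to be reported with it.
- **The power gain rests on assumptions.** The grade splits and the common odds ratio are not in the protocol, and other patterns remove or reverse the advantage. This objection stands in full.

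**Conclusion.** The point holds as a matter of fit and efficiency. On its natural reading the protocol compares ordered grades with a test that ignores their order. That test is valid and keeps its 5% error rate, but it does not target a shift toward better grades.

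If the benefit is spread over all grades with an odds ratio near 2.15, the loss is about 17 percentage points of power at 75 per arm (54-57% v 72-74%) and about 16 at 83. These figures depend on assumed control splits and on borrowing the 65% and 80% from the sample size section. It would be wrong to conclude that the rank sum test always does better: the gain is small for a partial shift and reverses (47% v 19%) when all benefit sits between the two lowest grades. It would also be wrong to call the planned test invalid.

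This is a cheap improvement to a secondary outcome, of minor to moderate importance.

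**What to change.** In section 2.8.3 add a sentence to this effect: the four TCM grades will be compared between arms by the Wilcoxon rank sum test, with a common odds ratio and 95% CI from a proportional-odds model as the effect estimate; the two-level effective rate (reduction of at least 30% v less) will be reported with its chi-square test as a supporting result. Chi-square stays in place for unordered categories.

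The cost is one sentence. No new data are needed, SPSS can run the analyses, and the rank sum test is already in the plan for other data. Section 4 states that recruitment had not begun when the manuscript was submitted, so the choice could be fixed before any outcome was seen. The downside is lower power than chi-square if the benefit is confined to one cut. If that cut is the one between the two lowest grades, the two-level rate would show it (about 54% power at 75 per arm).

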**Methods/design::**

This pragmatic randomized controlled trial will recruit 166 patients who are diagnosed with CP/CPPS. Simple randomization to conventional drug treatment with a 1:1 allocation ratio will be used. Ten 30-minute acupuncture sessions will be provided to patients assigned to the Intervention group. All participants will continue to receive conventional drug treatment. The selection of outcomes will be evaluated by Health's Symptom Score Index (NIH-CPSI) score at week 4.

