### Study design and settings

2.1

A brief flowchart of the entire study is shown in Figure 1. We will perform a 2-group, randomized, single-blind, placebo-controlled, multi-center trial that will evaluate the efficacy and safety of acupuncture for patients with CP/CPPS. This study will use a completely random grouping and parallel control observation design method. We will ensure the balance of the baseline data of the two groups through a sufficient sample size and a completely randomized grouping method. This study will be approved by the Ethics Committee of Dongzhimen Hospital Affiliated to Beijing University of Chinese Medicine. We will not begin recruiting at other centers in the trial until local ethical approval has been obtained. This study is registered at http://www.chictr.org.cn/showproj.aspx?proj=35685 (ChiCTR1900021132).The protocol includes elements recommended in the Standard Protocol Items: Recommendations for Interventional Trials checklist (Additional file 1).

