### Primary outcomes

2.6

The National Institutes of Health's Symptom Score Index (NIH-CPSI) score for CP/CPPS will be used as the primary outcome measure. Every dimensions (degree of pain, urinary symptoms, quality of life) of NIH-CPSI will be evaluated, and the lower the total score, the lighter the clinical symptoms of the patient.

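### The between-group test depends on a normality pre-test or on how the data are classed, none of the tests adjusts for baseline, and none is tied to the week-4 NIH-CPSI total

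*Protocol article*

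**What the plan says.** The primary outcome is set in section 2.6: the NIH-CPSI "score for CP/CPPS will be used as the primary outcome measure". The same section adds that "Every dimensions (degree of pain, urinary symptoms, quality of life) of NIH-CPSI will be evaluated" and explains how the total score is read. The abstract gives the time point: "The selection of outcomes will be evaluated by Health's Symptom Score Index (NIH-CPSI) score at week 4".

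Section 2.8.3 sets the tests by type of data:

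- For measurement data, "The normality of the measurement data is tested". Then "The data obeying the normal distribution is Student's t test", and otherwise "The data not obeying the normal distribution is rank sum test".
- For repeated measurements, the within-group comparison is repeated-measures analysis of variance, and "inter-group comparison is by multivariate analysis of variance (MANOVA").

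The section names no covariate and does not say which of these tests applies to NIH-CPSI. On baseline, section 2.1 says: "We will ensure the balance of the baseline data of the two groups through a sufficient sample size and a completely randomized grouping method".

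**The concern.** These are stated choices, not details left for an analysis plan. A later plan that named one baseline-adjusted analysis would depart from section 2.8.3.

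Two things are at stake.

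1. **What is estimated.** A symptom score taken before and after treatment fits both of the section's headings, measurement data and repeated measurement data. Its analysis could therefore be a t test, a rank sum test or a MANOVA. The first two are separated by a test on the trial's own data, the third by how the data are classed. With a P value threshold as the only decision rule, more than one result could be presented as the primary one.
2. **Precision.** The baseline value of a symptom score usually predicts the later value. None of the three tests uses it as a covariate. Section 2.1 relies instead on sample size and complete randomisation to secure balance, which they cannot guarantee.

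**Working it through.** **What each test delivers**

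| Test in section 2.8.3 | When it applies | What it gives |
|---|---|---|
| Student's t | normality not rejected | difference in means |
| Rank sum | normality rejected | comparison of rank distributions, no mean difference |
| MANOVA | data classed as repeated | omnibus P value over a set of responses, no week-4 difference |

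Only the first yields a mean difference at week 4, so the effect measure is not fixed in advance.

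**Inputs**

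- Evaluable patients: n = 75 per arm; randomised: 83 per arm (section 2.8.1). These are taken as the planned numbers. The sample size formula printed there does not reproduce 75: reading the divisor as 0.15 squared, 10.5 × (0.16 + 0.2275) ÷ 0.0225 = 180.8. That is a separate error and does not affect this comparison of methods.
- Two-sided alpha 0.05 and beta 0.10, so 90% power (section 2.8.1).
- Correlation r between baseline and week-4 NIH-CPSI: not given. Assumed 0.3, 0.5 and 0.7.
- No SD for NIH-CPSI is given, so differences are in SD units.

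**Unadjusted t test.** The normal approximation is (1.960 + 1.282) × √(2/75) = 0.529 SD. The noncentral t distribution with 148 degrees of freedom gives 0.533 SD.

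**ANCOVA.** The residual variance is multiplied by 1 − r², so the detectable difference is 0.533 × √(1 − r²).

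**MANOVA on baseline and week 4.** This is Hotelling's T² with two responses, no true difference at baseline and d at week 4. The noncentrality is (75 × 75 ÷ 150) × d² ÷ (1 − r²) = 37.5 × d² ÷ (1 − r²), on 2 and 147 degrees of freedom. 90% power needs a noncentrality of 12.92, so d = √(12.92 ÷ 37.5) × √(1 − r²) = 0.587 × √(1 − r²).

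| Assumed r | 1 − r² | Unadjusted t | ANCOVA | MANOVA (baseline, week 4) |
|---|---|---|---|---|
| 0.3 | 0.91 | 0.53 | 0.51 | 0.56 |
| 0.5 | 0.75 | 0.53 | 0.46 | 0.51 |
| 0.7 | 0.51 | 0.53 | 0.38 | 0.42 |

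ANCOVA cuts the variance by 9%, 25% and 49%. It detects a smaller difference than either alternative at every correlation shown. The MANOVA is worse than the t test at r = 0.3 and better at 0.5 and 0.7, and at no correlation does it estimate the week-4 difference.

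**Baseline balance.** With 83 randomised per arm, the standard error of a standardised baseline difference is √(2/83) = 0.155. The chance that it exceeds 0.2 SD in either direction is 2 × P(Z > 0.2 ÷ 0.155) = 0.20.

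**The case against.** The best defence is that section 2.8.3 sorts tests by data type, and a natural reading sends a repeatedly measured NIH-CPSI to MANOVA and single-time measures to the t or rank sum test. The visit schedule in Table 1, which is not shown, might settle this. In a condensed article, the covariates, contrast and confidence interval may also sit in an analysis plan. This narrows the ambiguity but does not remove it. If MANOVA is the intended test, it still gives no week-4 estimate; if it is not, the normality gate decides.

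A reader might infer four stronger points, which the document does not support:

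- **That the baseline score is wasted.** This is true of a t or rank sum test on week-4 scores. If baseline is one of the MANOVA responses, it is used, only less efficiently than as a covariate.
- **That chance imbalance biases the result.** It does not. Under randomisation the unadjusted standard error already allows for it, and the type I error rate holds.
- **That MANOVA breaks the Full Analysis Set by dropping patients with a missing visit.** That depends on imputation rules and visits not shown. A week-4 ANCOVA would also lose patients without a week-4 score unless values are imputed.
- **That within-group P values will be used as evidence for acupuncture.** Section 2.8.3 separates within-group from between-group comparisons and nowhere says this.

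**Conclusion.** The point holds as one about an undefined effect estimate and avoidable loss of precision, not about validity. The article prescribes a data-driven choice of test and an omnibus, unadjusted MANOVA, and ties none of them to the week-4 NIH-CPSI total.

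The gain from baseline adjustment ranges from small (0.53 to 0.51 SD at r = 0.3) to large (0.53 to 0.38 SD at r = 0.7). The size rests on assumed correlations and on 75 evaluable patients per arm. The lack of a single defined estimate rests on neither. That baseline NIH-CPSI is collected is inferred from the references to baseline data and repeated measurements, because Table 1 is not shown. The statement in section 2.1 that balance is ensured is wrong as worded, since a baseline difference above 0.2 SD has about a 20% chance.

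**What to change.** - In section 2.8.3, name one primary analysis: ANCOVA of the week-4 NIH-CPSI total on arm, adjusted for the baseline NIH-CPSI total, reporting the adjusted mean difference with a 95% confidence interval.
- If there are intermediate visits, use instead a mixed model for repeated measures with the same baseline covariate and the week-4 contrast as primary.
- Drop the normality gate, keep a rank-based test as a sensitivity analysis, and remove MANOVA as the between-group test.
- In section 2.1, say that randomisation leaves any baseline imbalance to chance, not that it ensures balance.

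The cost is wording only. The trial status section says recruitment had not begun at submission, SPSS fits both models, and no new data are needed if baseline NIH-CPSI is already recorded. That should be confirmed against Table 1.

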### Quality control and trial management

2.9

The management structure will comprise the principal investigator (PI), a trial management group, and a data monitoring committee. The trial management group will be responsible for conducting the trial and will meet monthly to discuss the trial progress. The PI will visit each collaborative hospital for face-to-face meetings and to share information to promote patient recruitment. The data monitoring committee will review safety and efficacy data. All data will be monitored every month through a central monitoring method. Additional monitoring may be performed at the discretion of the monitoring manager. The data monitoring committee have met once prior to the start of patient recruitment. At least twice per year, participating investigators, research assistants, and research nurses will be required to attend a training workshop on clinical research to ensure strict adherence to the study protocol and familiarity with the trial administration process. The data collected in this trial will comprise information recorded in case report forms and questionnaires. Data quality will be checked regularly by research assistants and overseen by monitors; all modifications will be marked on case report forms and data managers will recheck the data before they are officially logged. The database will be locked after all data have been cleaned. If participants withdraw from the trial during the study period, the reasons will be documented and the dropout rate will be statistically analyzed.

### Feasibility analysis

2.10

The hospital has formulated related systems, such as scientific research organization management, to provide guarantee measures for the organization and management of the subject. In strict accordance with the relevant requirements of the superiors, the financial department is responsible for management and supervision, and establishes accounts according to items, which are used exclusively by the project team. Carry out research as planned, actively accept the guidance and supervision of relevant higher-level management departments, and submit the Annual Summary Report on the Implementation of Scientific Research Projects to management departments every year. The Scientific Research Department is responsible for the daily management during the implementation of the project, helping to solve practical difficulties, inspecting and supervising the research progress, and establishing subject files; major personnel changes and major changes in research plans and programs must be reported to the superior management department Approval. In order to ensure that the team leader and members have enough time and energy to devote themselves to the research, the college has formulated related systems and strictly implemented the responsibility system for the team leader.

## Discussion

3

The etiology of CP/CPPS is complex, and its pathogenesis has not been fully elucidated so far. There are reports in the literature that there is some connection between prostate hyperplasia and CP / CPPS. Modern medicine does not have a clear treatment plan for CP/CPPS.^[13]^ At present, antibiotics and alpha blockers are often used for treatment. In recent years, clinicians have gradually realized the heterogeneity of chronic prostatitis, that is, different people have different etiology, different clinical manifestations, different disease processes and different responses to treatment.^[14,15]^ In addition, due to the special nature of the prostate anatomy—the inner membrane is deeply wrapped, it is easy to cause local microcirculation disturbance, drainage is blocked, the drug is difficult to reach the lesion, and it is unable to fully achieve the effect.^[16]^ important reason. Therefore, in the treatment of chronic prostatitis, while emphasizing comprehensive treatment, more and more attention is paid to individualized treatment, and treatment options are selected based on individual specific clinical manifestations. Chronic prostatitis / chronic pelvic pain syndrome (CP/CPPS) accounts for 90% to 95% of prostatitis.^[17,18]^ Although there are many treatments for CP / CPPS, there are no specific treatments, and the treatment results are not satisfactory.^[19]^ Lack of a unified and standardized treatment plan.

At present, oral medication for chronic prostatitis is the most important treatment method, and the effect is significant. However, there are some intractable problems with oral medication, such as higher treatment costs, longer treatment periods, and long-term gastrointestinal stimulation in patients. This leads to many patients not being able to adhere to treatment, which ultimately affects the clinical efficacy, and even leads to the loss of previous achievements. It is therefore important to explore new treatment options. Therefore, we will evaluate the clinical effectiveness and safety of acupuncture in the treatment of CP/CPPS. We hope that the results of this study will provide clinicians with the basis for acupuncture treatment of CP/CPPS and more treatment options.

